## Abstract

**Background:**

Parkinson’s disease (PD) is a neurodegenerative condition that impacts motor planning and control of the upper limbs (UL) and leads to cognitive impairments. Rehabilitation approaches, including motor imagery (MI) and action observation (AO), along with the use of brain-machine interfaces (BMI), are essential in the PD population to enhance neuroplasticity and mitigate symptoms.

**Objective:**

To provide a description of a rehabilitation protocol for evaluating the effects of isolated and combined applications of MI and action observation (AO), along with BMI, on upper limb (UL) motor changes and cognitive function in PD.

**Methods:**

This study provides a detailed protocol for a single-blinded, randomized clinical trial. After selection, participants will be randomly assigned to one of five experimental groups. Each participant will be assessed at three points: pre-intervention, post-intervention, and at a follow-up four weeks after the intervention ends. The intervention consists of 10 sessions, each lasting approximately 60 minutes.

**Expected results:**

The primary outcome expected is an improvement in the Test d’Évaluation des Membres Supérieurs de Personnes Âgées score, accompanied by a reduction in task execution time. Secondary outcomes include motor symptoms in the upper limbs, assessed via the Unified Parkinson’s Disease Rating Scale - Part III and the 9-Hole Peg Test; cognitive function, assessed with the PD Cognitive Rating Scale; and occupational performance, assessed with the Canadian Occupational Performance Measure.

**Discussion:**

This study protocol is notable for its intensive daily sessions. Both MI and AO are low-cost, enabling personalized interventions that physiotherapists and occupational therapists can readily replicate in practice. While BMI use does require professionals to acquire an exoskeleton, the protocol ensures the distinctiveness of the interventions and, to our knowledge, is the first to involve individuals with PD.

**Trial registration:**

ClinicalTrials.gov NCT05696925.

## Introduction

Parkinson’s Disease (PD) is a complex neurodegenerative disorder characterized by both motor and non-motor symptoms, progressively incapacitating the individual [1]. PD leads to impairments in motor skills, with multiple manifestations including tremor, rigidity, bradykinesia, and postural instability [2,3]. In the upper limbs (UL), PD negatively affects motor control and planning, resulting in disturbances in dexterity and both gross and fine motor skills, which interfere with the execution of daily activities, such as maintaining self-care, performing productive tasks, and participating in leisure activities [1,4].

Additionally, there is a relationship between the motor symptoms of the UL and cognitive demand, revealing deficits in reach, grasp, and action speed [5]. The greater the motor impairment in the UL, the more significant the impairment in performing cognitive tasks [6]. This raises concerns given the prevalence of dementia and mild cognitive impairment in PD, with issues spanning several domains, including concentration and attention, working memory, recent events, as well as difficulties with calculations, spatial orientation activities, and executive functions [1,7,8]

In light of these disabling symptoms, there has been a focus on incorporating additional approaches to optimize rehabilitation gains which aim to maximize movement quality through personalized interventions linked to the stage of PD progression [9], such as motor imagery (MI) and action observation (AO) [10]. MI involves the mental rehearsal of motor acts, where the individual simulates motor actions and sensations internally [11]. To enhance the neuroplasticity promoted by MI, the brain-machine interface (BMI) emerges as a new technology that decodes neural signals in real-time via electroencephalogram (EEG) during MI practice, activating external devices such as prosthetics or robots and providing instant feedback to the attached limb [12].

AO is a technique based on the activation of the mirror neuron system, referring to a group of neurons distributed throughout the cerebral cortex that activate similarly when observing an action and when executing it. Thus, by observing an action, the brain can map the movement, creating a motor representation and executing it internally, thereby acquiring knowledge and motor memory [13,14]. Both AO and action execution (AE) can promote motor learning, facilitating cortical reorganization and restoring cognitive references. However, there is no detailed description of the protocols applied for these techniques [15].

Therefore, due to the motor impairments caused by PD in the UL and the accompanying cognitive function deficits, along with the scarcity of studies involving MI, AO, and BMI - both individually and as combined techniques in PD - and the lack of detailed descriptions of the applied protocols, there is a clear need for additional research to develop innovative rehabilitative approaches and further reinforce the existing evidence with larger studies. Hence, this protocol study aims to provide a description of the rehabilitation protocol that can be utilized to evaluate, through a simple blinded randomized controlled clinical trial, the effects of the isolated and combined application of MI and AO, along with BMI, on motor alterations in the UL and cognitive function in PD.

## Methods

### Study design

This is a description of a protocol for a simple blinded randomized clinical trial to evaluate the effects of the application of MI, AO, and BMI, either individually or in combination, on motor alterations in the UL of individuals with PD. All participants will be evaluated pre-intervention (T0) and post-intervention (T1), and will undergo a follow-up (T2) four weeks after the end of the intervention.

The clinical trial was designed following the Consolidated Standards of Reporting Trials (CONSORT) [16]. The protocol follows the item definitions for clinical trials as per the Standard Protocol Items: Recommendations for Interventional Trials - SPIRIT [17] (S1 Checklist).

### Study setting

The data will be collected on the premises of the Federal University of Health Sciences of Porto Alegre, in Porto Alegre, Brazil.

### Ethical aspects

The study is registered on clinicaltrials.gov with the study ID number: NCT05696925 (S3 File). The project was approved by the Research Ethics Committee of the Federal University of Health Sciences of Porto Alegre (UFCSPA), under letter nº 5.638.729, and received the Certificate of Ethical Appreciation Presentation (CAAE) number 61710822.0.0000.5345 (S1 File and S2 File).

To be included, volunteers must read and sign the Informed Consent Form. The entire research was written following Resolution 466/2012 of the Brazilian National Board of Health, and adhered to the principles of the Declaration of Helsinki for research involving human subjects. Data will be processed in accordance with the General Data Protection Law (Brazilian Law nº 13.709/2018).

All researchers are aware of and agree to maintain the confidentiality of personal information about participants that will be collected, shared, and maintained before, during, and after the trial, having signed the Confidentiality Agreement submitted along with the UFCSPA Ethics Committee, and access to the final dataset of the trial will be limited solely to the researchers.

### Eligibility criteria

#### Inclusion criteria.

Have a diagnosis of PD and be at stages 1–3 on the Hoehn and Yahr scale [18]; be at least 20 years old; be on stable medication; achieve a score higher than 23 on the Montreal Cognitive Assessment (MoCA) [19]; score a minimum of 20 points on the Kinesthetic and Visual Imagery Questionnaire (KVIQ-10) [20,21]; exhibit motor impairment in the dominant UL, with scores above average according to manual dominance and sex in the 9-Hole Peg Test (9HPT) [22]; and have signed the Informed Consent Form.

#### Exclusion criteria.

Having additional central nervous system disorders or other conditions that could affect upper and lower limb function; having other uncontrolled chronic conditions that may interfere with participant safety; and not be using deep brain stimulation (DBS) devices.

### Participant timeline

The schematic diagram (Fig 1) outlines the overall timeline and engagement duration for participants in the trial, detailing the time allocated for each phase, starting from the initial eligibility screening to the conclusion of the study. It includes the time periods during which the trial interventions will be administered, as well as the procedures and assessments conducted in each phase.

**Fig 1 pone.0315148.g001:**
[figure not shown]
SPIRIT schedule of enrolment, interventions, and assessments of the study. COPM, Canadian Occupational Performance Measure; H&Y, Escala Hoehn **e** Yahr; KVIQ-10, Kinesthetic and Visual Imagery Questionnaire; MoCA, Montreal Cognitive Assessment; PD-CRS, Parkinson’s disease-cognitive rating scale; t, time; TEMPA, Test D’évaluation Des Membres Supérieurs Des Personnes Âgées; UPDRS, Unified Parkinson’s Disease Rating Scale; 9HPT, Nine Hole Peg Test.

### Randomization, allocation and blinding

Following selection, participants will be randomly allocated into one of five experimental groups: GE1 (motor imagery, action observation, and action execution), GE2 (motor imagery and action execution), GE3 (action observation and action execution), GE4 (motor imagery via brain-machine interface and action execution), and GE5 (motor imagery via brain-machine interface, action observation, and action execution) (Fig 2).

**Fig 2 pone.0315148.g002:**
[figure not shown]
Flowchart of participant distribution throughout each stage of the study. AO, action observation; BMI, brain machine interface; AE, action execution; EG, experimental group; MI, motor imagery.

Allocation will be carried out by a blinded investigator who will not be involved in the intervention. The randomization process will be carried out with a 1:1 allocation ratio through the website randomizer.com. It will not be possible to blind the participants and researchers who will carry out the training. However, the study will be blinded to the researchers for results and statistical analysis. This is a single-blind study, as the therapists (physical and occupational therapists) conducting the interventions will be different from those responsible for administering the assessment tools during data collection phases. Additionally, the blinding of data analysis will be ensured.

### Data collection

The following instruments will be used for pre-intervention (T0) and post-intervention (T1) assessments. The Test d’Évaluation des Membres Supérieurs de Personnes Âgées (TEMPA) will be employed to evaluate limitations of the UL through tasks that simulate activities of daily living [23]. The final score of the test, which can reach up to 186 points, corresponds to the sum of the functional score, encompassing unilateral and bilateral tasks (totaling up to 36 points), and the task analysis score, which assesses five areas of sensory and motor skills in the UL (totaling up to 150 points). In this study, unilateral tasks will be performed using the more affected UL. For better interpretation, especially in task analysis, sessions will be recorded for subsequent analysis.

To assess fine manual motor performance, the 9-Hole Peg Test (9HPT) will be administered, considering the average times based on sex and manual dominance: for men, 21.1 seconds for the dominant hand and 22.3 seconds for the non-dominant hand; for women, 19.9 seconds for the dominant hand and 21.4 seconds for the non-dominant hand [22]. This instrument will be used as a screening tool, and data from included participants will be analyzed in the final results.

To evaluate motor disturbances in PD, the Unified Parkinson’s Disease Rating Scale - part III (UPDRS-III) will be utilized, which involves motor assessment [24], excluding items related to facial symptoms or those corresponding to motor symptoms in the lower limbs. The maximum score is 32 points, with higher scores indicating worse symptoms.

Cognitive functions will be assessed using the Parkinson´s disease -Cognitive Rating Scale (PD-CRS), which encompasses nine functions: sustained attention, working memory, immediate and delayed verbal memory recall, alternating verbal fluency, action verbal fluency, spontaneous clock drawing, visual confrontation naming, and clock drawing copying. The total score for the PD-CRS is 134 points [25].

The Canadian Occupational Performance Measure (COPM) is a semi-structured interview that identifies problem activities in the areas of self-care, productivity, and leisure. For this study, participants will choose up to five problem activities, rating them from 1 to 10 based on their performance and satisfaction [26]. In cases of motor symptoms in the non-dominant UL, participants will be instructed to select problem activities that involve more bimanual actions.

In addition to the previously mentioned instruments, the researchers will ask participants about their perception of severity with the following questions: 1) “How would you rate the severity of your upper limb motor functions (dexterity, speed, movement precision)?”; 2) “How would you rate the severity of your cognitive functions (memory, attention, concentration, organization)?”. Participants will respond using a Likert scale: none, mild, moderate, severe, and extreme.

For the follow-up assessment (T2), conducted four weeks after the completion of the interventions, the COPM will be reapplied, along with the questionnaire regarding the perception of severity of motor and cognitive functions.

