### Interventions

Each participant will undergo the first stage of data collection, the pre-test (T0), which will take place one day before the treatment period begins. This stage will consist of the administration of the four assessment instruments. Additionally, on this same day, participants assigned to the GE4 and GE5 groups will experience the interventions to familiarize themselves with how they will be conducted throughout the treatment.

The next stage involves the actual intervention. Regardless of the allocated group, all participants will undergo 10 treatment sessions, with each session lasting approximately 60 minutes. The entire study process will span a period of two weeks, with a two-day interval in the middle [27].

It is important to note that the activities to be imagined, observed, and executed during the interventions will be pre-selected by the therapist based on the participant’s preferences indicated through the COPM. The choice of activity will also depend on the dominance of the affected limb; if the dominant side is more affected, the activity will preferably be unilateral. However, if the more affected side is the participant’s non-dominant side, the activity will necessarily be bilateral. To ensure equal application of the interventions across all experimental groups, the techniques will be administered by the same therapist according to the following protocol:

#### 
Motor imagery (MI).

The activities will be narrated by the therapist during the intervention, guiding the participant - eyes closed and seated - to imagine executing the action from a first-person perspective, without the presence of motor symptoms and without performing any actual movement. To facilitate imagination, the participant may hold or grasp a real object related to the activity being imagined, either before or during the imagery, serving as a sensory stimulus for motivation. At the end of each imagined activity, the therapist will ask the participant whether they were able to imagine themselves performing the requested activity without motor symptoms. Each imagery session will last approximately 2 minutes.

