**Fig 4 pone.0315148.g004:**
[figure not shown]
Sequence of applicability of interventions. AO, action observation; BMI, brain machine interface; AE, action execution; EG, experimental group; MI, motor imagery.

During the intervention sessions, the difficulty of tasks may be adjusted as the participant progresses in execution, by altering the objects used in the activities, such as sizes, weights, resistances, and different shapes, to change the types of grips and pinches, as well as the range of motion, in addition to being prompted to perform as quickly as possible to stimulate movement speed. It is crucial that the environment is free from distractions to promote concentration during the sessions. Additionally, to ensure proper EEG recording, participants will be advised not to attend sessions with wet hair.

After the intervention period, each participant will undergo the second data collection phase, the post-test (T1), which will take place the day after completing the 10 intervention sessions. This phase will involve the administration of the same four evaluation instruments applied at T0, along with the 9HPT. On this day, participants will also be reminded of the third data collection phase, the follow-up (T2), scheduled to occur four weeks after the conclusion of the interventions. In the follow-up, participants will receive a call and will again respond to the COPM, reporting their satisfaction and performance regarding the problem activities, as well as completing a questionnaire on their perception of the severity of motor and cognitive functions (S1 Graphycal abstract).

Below are some sequences of images as examples of activities recorded on video for the AO. Three activities will be described, each involving an area of occupational performance: self-care, productivity, and leisure, detailed with technical descriptions of the executed movements and a narrative manner involving verbal commands for MI. Here are the examples:

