### Outcome

As the main outcome of the study, an improvement in the TEMPA score is expected, along with a decrease in the execution speed of tasks, indicating that participants experienced positive impacts on upper limb motor symptoms after interventions involving action observation, motor imagery, and brain-machine interface. As for secondary outcomes, improvements in motor symptoms are anticipated, evidenced by lower scores on the UPDRS-III and reduced time in the 9 Hole-Peg Test, as well as enhancements in cognitive symptoms indicated by increased scores on the PD-CRS. Additionally, it is expected that the interventions will also have a positive effect on occupational performance, leading to better performance and satisfaction in daily activities as assessed by the COPM. The averages of the assessments will be considered, with measurements for each outcome taken at T0 and T1, and at T2 regarding perceptions of changes in motor and cognitive conditions, as well as the COPM.

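### The protocol contradicts itself on whether the 9HPT is measured at T0; if the screening value serves as baseline, regression to the mean biases the pre-post 9HPT result

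*Protocol article*

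**What the plan says.** - **Entry rule (Inclusion criteria).** Participants must "exhibit motor impairment in the dominant UL, with scores above average according to manual dominance and sex in the 9-Hole Peg Test (9HPT"). Data collection gives the reference averages: "for men, 21.1 seconds for the dominant hand" and "for women, 19.9 seconds for the dominant hand".
- **Use of the screening test (Data collection).** "This instrument will be used as a screening tool, and data from included participants will be analyzed in the final results".
- **Timing, first version.** The opening line of Data collection introduces its instruments, the 9HPT among them, as those for T0 and T1. The Outcome section says every outcome is measured at T0 and T1.
- **Timing, second version (Interventions).** Of T0: "This stage will consist of the administration of the four assessment instruments". Of T1, in the text after Fig 4: "This phase will involve the administration of the same four evaluation instruments applied at T0, along with the 9HPT".
- **How the result is read.** The Outcome section counts "reduced time in the 9 Hole-Peg Test" as improvement. Statistical analysis tests the main effects of group and time and their interaction. All five randomised groups receive an active intervention.

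**The concern.** Data collection describes five scored instruments: TEMPA, 9HPT, UPDRS-III, PD-CRS and COPM. Taking the 9HPT away leaves exactly four, which fits the T0 and T1 descriptions in Interventions. On that reading, the only 9HPT value before treatment is the one that admitted the participant.

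A value admitted for lying above a cutoff carries positive measurement error on average. A second measurement does not, so it tends to be lower even if nothing has changed. The bias runs in the direction the protocol calls benefit, and no untreated arm shows how large a fall occurs without treatment. At stake is the pre-post 9HPT result, a named secondary outcome. TEMPA and the sample size are not affected.

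**Working it through.** **1. The passages side by side**

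| Place | 9HPT at T0? |
|---|---|
| Data collection, opening line | Yes, by listing |
| Outcome, last sentence | Yes, by the general statement on all outcomes |
| Interventions, T0 paragraph | Four instruments, not named |
| Interventions, T1 paragraph | No: the 9HPT is additional to the T0 four |

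No passage describes a second 9HPT between screening and treatment. The schedule figure is not available here.

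**2. Number analysed**

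The plan's 95 participants include a 19% margin: 95 / 1.19 = 79.8, so about 80 completers. A noncentral F calculation for the interaction (f = 0.2, five groups, two assessments, alpha 0.05, 80% power) also gives N = 80, with power 0.803, if the correlation between assessments is 0.5. The plan does not state that correlation. Then 80 × 1.19 = 95.2, which reproduces the 95.

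**3. Inputs for regression to the mean**

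- Cutoff c = 20.5 s, the midpoint of the dominant-hand averages: (21.1 + 19.9) / 2.
- Assumed, because the documents give none of them: mean m of 22 to 28 s and SD s of 4 to 8 s among people screened, and retest reliability r of 0.7 to 0.9.
- Also assumed: the outcome uses the dominant hand, times are normally distributed, and there is no treatment or practice effect.

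**4. Formulas**

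Let a = (c − m)/s and h = φ(a)/(1 − Φ(a)).

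- Expected fall = s(1 − r)h
- Variance of the change = (1 − r)²s²(1 + ah − h²) + s²(1 − r²)
- z = fall / (SD of change / √80)
- False-positive rate = P(|Z + z| > 1.96), with Z standard normal

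**5. Worked corners**

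- m = 22, s = 8, r = 0.7: a = −0.188, h = 0.682. Fall = 8 × 0.3 × 0.682 = 1.64 s. SD of change 5.91 s, z = 2.48, rate 70%.
- m = 28, s = 4, r = 0.9: a = −1.875, h = 0.071. Fall = 4 × 0.1 × 0.071 = 0.03 s. SD of change 1.78 s, z = 0.14, rate 5%.

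| Mean / SD (s) | Fall (s) at r = 0.7, 0.8, 0.9 | False-positive rate |
|---|---|---|
| 22 / 4 | 0.69, 0.46, 0.23 | 55%, 39%, 21% |
| 22 / 8 | 1.64, 1.09, 0.55 | 70%, 51%, 28% |
| 26 / 6 | 0.58, 0.38, 0.19 | 21%, 15%, 10% |
| 28 / 4 | 0.09, 0.06, 0.03 | 6%, 5%, 5% |
| 28 / 8 | 0.75, 0.50, 0.25 | 20%, 15%, 10% |

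Simulation of the paired t test (4000 trials per setting, n = 80) agrees with these rates to within about one percentage point.

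**6. Which analyses are affected**

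A second simulation used five groups of 16, a cutoff of 21.1 s and the F tests of the mixed ANOVA. With the screening value as baseline, the time effect was falsely significant in 6.4% (mean 30, SD 6, r = 0.9) to 64% (mean 21, SD 6, r = 0.8) of trials. The group-by-time test stayed at 4.5% to 5.4%. With a separate baseline taken after eligibility, the time effect returned to 4.4% to 5.4%.

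**The case against.** **The premise is contested.** A reader might infer from Interventions that the screening value definitely is the baseline. The documents do not establish that. Data collection and Outcome both point to a T0 measurement, and the schedule that might settle it cannot be seen. This objection stands: what is certain is the contradiction, and the bias depends on how it is resolved.

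**The size is unknown.** A reader might also infer that the pre-post result would often be falsely positive. That is not supported. The high rates need candidates averaging close to the cutoff. If most candidates are much slower than the cutoff (28 / 4 in the table), there is essentially no inflation. Nor does a stable 9HPT make the problem worse: at a fixed SD, higher reliability shrinks the spurious fall as well as the variance of the change, and the rate drops.

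**The hand is not stated.** Selection is on the dominant hand, but the protocol allows the non-dominant side to be the more affected one and does not say which hand gives the outcome. A non-dominant value was not directly truncated, so the calculation would not apply as run.

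**The consequence is limited.** This is a secondary outcome, and the randomised comparison is unbiased because every arm passes the same cutoff. With five active arms, a change over time cannot be attributed to treatment anyway. That is true, but the protocol does present reduced 9HPT time as evidence of benefit and does test the time effect, so the error rate of that test matters.

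**Conclusion.** The contradiction over the 9HPT baseline is in the text and needs to be resolved. If the Interventions section is followed, the main effect of time and any within-group pre-post claim for the 9HPT are biased towards improvement. Under the assumptions listed, the spurious fall is about 0.03 to 1.6 s and the false-positive rate about 5% to 70%, against about 5% with a separate T0 baseline. That range includes no inflation at all, and the documents do not allow it to be narrowed. The group-by-time comparison, the primary outcome and the sample size are unaffected. The point should be corrected, but it does not undermine the trial's main comparison.

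**What to change.** 1. Amend the T0 and T1 descriptions in Interventions to list the 9HPT at T0, in line with Data collection and Outcome.
2. State that the screening 9HPT decides eligibility only and that the T0 value is the baseline for analysis. State which hand is analysed.
3. Recruitment began in February 2023, so some participants may have only a screening value. For them, compare T1 9HPT between arms with adjustment for the screening value, and make no pre-post claim.

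The cost is one brief repeat of an existing test at an existing visit, plus wording; the third step needs no new data. A separate baseline removes regression to the mean, but it does not make a pre-post change causal, because all five arms are active. Conclusions about treatment should rest on the between-arm comparison.
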